#### 11.1.2 Immunological components

Serological assays will involve all cohort participants. Detailed immunological assays such as the chemo/cytokine panel and T and B cell response will be conducted from the stored samples of approximately 45 malaria cases and a similar number of matched malaria negatives per country, i.e., approximately 90 per country or 180 overall. The sample size may increase if more funding becomes available.

### 11.1.3 Nested malaria treatment trial

Approximately 54 participants in Kenya are expected to have malaria (15% of 354) and will be enrolled in the nested treatment study comparing AL vs pyronaridine-artesunate (1:1). The corresponding number in Burkina Faso is 88 (25% of 354). Thus 142 pooled across the two countries. A study of 142 participants has 80% power to detect a 22.2% absolute increase in viral clearance by day-7 from 20% in the artemether-lumefantrine arm to 42.2% in the pyronaridine-artesunate arm ( $RR=2.11$ ), assuming a 5% loss to follow-up by day 7 (134 completers) (two-sided  $\alpha=0.05$ ). The 20% viral clearance rate by day=7 in the control arm (artemether-lumefantrine) is based on a previous trial.

Similarly, a sample of 142 participants has 80% power to detect a 50% relative decrease ( $RR=0.50$ ) or increase ( $RR=1.50$ ) in the cumulative seroconversion rate by day 14 from 50% in the artemether-lumefantrine arm (control arm) to either 25% or 75% in the pyronaridine-artesunate arm, assuming a 10% loss to follow-up (128 completers). The seroconversion rate of 50% by day 14 is based on previous observational COVID-19 studies in China.

Although the nested malaria treatment trial will be exploratory in nature, the study design includes the option to conduct interim analyses as part of the emergency response to the pandemic to ensure that promising findings can be shared early (see 11.2.5.3, Interim analysis and early stopping rule for efficacy, page 59).

### 11.1.4 Screening study (cross-sectional survey source population)

A source population of 4,720 suspected cases (2,360 in each country) is required to recruit a cohort of 708 participants (354 per country). This assumes a SARS-CoV-2 test positivity rate of 20% across the two countries and eligibility of 75% among those testing positive ( $0.2 \times 0.75 \times 4,720 = 708$ ). If the average malaria RDT test positivity in the source population is 20% across both countries pooled, then 4,720 suspected cases would consist of 234, 710, 710 and 3066 MAL+/C19+, Mal+/C19-, MAL-/C19-, and MAL-/C19- participants. Such a sample size with a ratio of 4:1 malaria-negative: malaria-positive participants would provide 80% power to detect a 25% difference from 18.6% to 23.3%, allowing for a 30% sample size inflation relative to a crude analysis that does not adjust for confounding (effective sample size of 3,630), or a 26% difference from 18.6% to 23.4% allowing for 35% sample size inflation (effective sample size 3,495) (two-sided  $\alpha = 0.05$ ).

### 11.1.5 Interim sample size re-estimations and feasibility of recruitment

This study is designed at a time when there are many uncertainties about the parameters needed for sample size calculations. A two-stage approach will be used that includes an 'internal pilot study' in approximately the first 20% of cases. This is then followed by a formal blinded interim sample size re-estimation to assess the test positivity for malaria and SARS-CoV-2 in the source population and the observed event and drop-out rate in the COVID-19 cohort study. The progression of the epidemic, malaria season and health system, and study site capacity will also be taken into account during the sample size re-estimation to determine the feasibility of the total sample size and if any potential expansion to more sites is required.

## 11.2 STATISTICAL ANALYSIS

### 11.2.1 General principles

All statistical analyses will be described in detail in the Statistical Analysis Plan (SAP). All tests will be two-sided and unless otherwise defined and  $P$ -values  $<0.05$  will be used to define statistical significance for analysis.

## 11.2.2 Populations for analysis

### 11.2.2.1 Screening study (cross-sectional survey source population) and COVID-19 cohort study

All participants in the screening study (cross-sectional survey, source population) and COVID-19 cohort study will contribute to the analysis of the associations with malaria and COVID-19 prevalence and severity.

### 11.2.2.2 Malaria treatment study

For the nested malaria treatment trial, the primary analyses will be based on the Intention-to-treat (ITT) population and secondary supportive analyses will be done on the Per-protocol (PP) population. The safety analysis will be performed on the safety population. These analytical populations are defined as follows: 1) The ITT population consists of all randomised subjects with valid informed consent; 2) The PP population is a subset of the ITT population, where subjects with major protocol deviations will be excluded. Major protocol deviations will be defined in the Statistical Analysis Plan (SAP). 3) The safety population is a subset of the ITT population, consisting of all randomised subjects who receive at least one dose or a partial dose of study drug.

## 11.2.3 Screening study (cross-sectional survey source population)

The primary analysis of the cross-sectional data is the estimation of malaria infection as a potential risk factor for COVID-19, adjusted for other predictors of COVID-19 prevalence. We will use log-binomial regression to obtain prevalence ratios (95% CI) of malaria among patients who test positive vs negative for SARS-CoV-2. The analysis will also be stratified by age groups and the presence of symptoms on enrolment. Similar approaches will be used for secondary analyses of the evaluation of other potential risk factors for COVID-19 and severity.

## 11.2.4 Analytical methods by type of endpoint measure

### 11.2.4.1 Binary endpoints

For single measurements of binary endpoints, including for the binary primary endpoints of the screening study (cross-sectional survey, source population), COVID-19 cohort study and the nested malaria treatment trial, a generalised linear model (GLM) with the log-link function and binomial distribution (log-binomial regression) will be used to compare endpoints between exposure groups (e.g. by malaria status at enrolment). Crude GLM models will have the predictor of interest (e.g. malaria status at enrolment) as the only predictor and 'study site' as covariates. Results will be expressed as the risk ratio (RR) with associated 95% CI. If the log-binomial regression models do not converge, the 'binreg' or 'difficult' options (in that order) will be specified in Stata. If all models fail to converge, log-Poisson regression with a sandwich variance estimator will be used. Because the effect of malaria on COVID-19 may be biased by predictors that are not equally distributed by other predictors of COVID-19 severity, such as age, we will also conduct adjusted analyses to determine whether the effect of malaria on COVID-19 is affected with the inclusion of additional covariables. For repeated measurements of binary endpoints, a generalised linear mixed model (GLMMIX) with the log-link function and binomial distribution (log-binomial regression) will be used.

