### 5.1.2 COVID-19 cohort study (N~708)

All SARS-CoV-2 positive participant from the source population will be eligible for enrolment in the COVID-19 cohort study of *confirmed* COVID-19 cases regardless of their malaria status. The COVID-19 cohort study has a clinical disease progression component and an immunological component. It also has a nested malaria treatment trial in a subgroup of participants that are co-infected with malaria (see 5.1.3, Nested malaria treatment trial within the COVID-19 cohort study, below). The primary aim is to determine if symptomatic or asymptomatic malaria infection affects the clinical course of COVID-19. Some elements of the immunological component involve all participants in the COVID-19 cohort study (e.g. antibody responses), and some involve a subset of approximately 180 participants (e.g. cellular responses) from whom more detailed immunologic profiling of serial samples of serum and whole blood will be analysed and compared between participants with and without malaria. All cohort participants will be followed on days 0, 3, 7, 14, and 28 to monitor disease progression, cumulative seroconversion rates, viral load, and viral carriage. Additional samples will be taken at 3, 6, and 12 months to determine the duration of the protective antibody responses to the SARS-CoV-2 virus.

All COVID-19 patients without malaria will be treated with the recommended standard of care (SOC) at the time of enrolment. The SOC will follow the national guidelines in each country and are subject to change (see 7.1.1, Interventions, COVID-19 cohort study, page 33). All COVID-19 patients with malaria will be enrolled in the nested malaria treatment trial and have additional samples taken at day 21 and day 42, as described in section 5.1.3, below.

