#### 11.1.1 Cohort

The primary endpoint used for the sample size calculations is the cumulative proportion of patients that progresses at least one category in disease severity from enrolment to day-28 based on the WHO clinical progression scale (see 16.4, Appendix IV. WHO clinical progression scale, page 82). At least one category increase in disease severity is defined as progressing from either asymptomatic or mild disease at enrolment to at least moderate disease requiring hospital admission (excluding hospitalisations for isolation only), or from moderate disease at enrolment to severe disease, or from severe disease at enrolment to death. For definitions of each disease severity category, see 16.4, Appendix IV. WHO clinical progression scale, page 82. The sample size calculations to determine the crude impact (i.e., unadjusted for potential confounders) of malaria on COVID-19 disease regression suggests that a pooled sample size of 708 (673 completers) of whom approximately 142 are malaria positive and 566 are malaria negative (135 and 538 completers) would provide 90% power to detect a 50% difference in the primary endpoint from 30% in the malaria-negative group to 45% in the malaria positive group ( $\alpha=0.05$ , 5% loss to follow-up by day 28). The true power is likely to be lower when the confounding effect of baseline differences between malaria and non-malaria patients (such as age is considered). However, the inflation in the sample size required is difficult to estimate a priori. Similar crude sample size calculations using 80% power suggest 522 participants are required. Thus overall, a sample size of 708 participants would provide 80% power to detect a 50% difference in the primary endpoint allowing for a 35.6% inflation in sample size ( $708/522=1.356$ ) to take adjustment for confounding into account in multivariate or stratified analysis. The sample size calculation for the COVID-19 cohort study assumes that each country will recruit 354 COVID-19 participants and that approximately 20% of them are coinfecting with malaria (RDT positive), representing a weighted average of 15% of 354 COVID-19 cases in Kenya and 25% of 354 cases in Burkina Faso.

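### The crude cohort models attribute any effect of pyronaridine-artesunate to malaria, chiefly on the viral and antibody endpoints, because up to half of the malaria-positive group is randomised to it

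*Protocol*

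**What the plan says.** Section 11.2.4.1 says that log-binomial regression will "compare endpoints between exposure groups (e.g. by malaria status at enrolment". The crude model contains that predictor and study site. Adjusted models may add further covariates, of which only age is named. Section 11.2.2.1 puts every cohort participant into the analysis. Treatment arm appears as a model term only in section 11.2.5.2, for the nested trial.

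Section 5.1.2 states that "All COVID-19 patients with malaria will be enrolled in the nested malaria treatment trial"; section 7 limits this to those who meet the eligibility criteria. Allocation is 1:1 (section 11.1.3). Malaria-negative participants receive standard of care only (section 7.1.1.1).

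The nested trial is sized to detect a rise in day-7 viral clearance "from 20% in the artemether-lumefantrine arm to 42.2% in the pyronaridine-artesunate arm". The cohort is sized to detect a rise in progression "from 30% in the malaria-negative group to 45% in the malaria positive group", on "a pooled sample size of 708 (673 completers) of whom approximately 142 are malaria positive and 566 are malaria negative (135 and 538 completers").

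**The concern.** The exposed group contains a treatment that the unexposed group does not receive. Section 3.2.3 gives the reason for testing PA: pyronaridine may act on SARS-CoV-2, possibly for 28 days, which is the cohort's endpoint window, while lumefantrine shows no antiviral activity in vitro. Sections 4.2 and 4.3 list largely the same outcomes for the two components: clearance, viral load, antibody response and severity.

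If PA affects one of these outcomes, a model with malaria status as its only exposure returns the malaria effect mixed with up to half of the PA effect. The cohort could then report that malaria speeds viral clearance or alters seroconversion when it does neither. On severity, a protective effect of PA would dilute a harmful effect of malaria or, with no malaria effect, make malaria look protective. Section 3.2.1 says that a protective finding would bear on aggressive malaria control.

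**Working it through.** **Method.** Two-sided test of two proportions with pooled variance, alpha 0.05 (section 11.1.1; section 11.2.1: "All tests will be two-sided"), no continuity correction:

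power = Φ[(|p1 − p0| − 1.96·s0)/s1], where s0 = √{p̄(1 − p̄)(1/n0 + 1/n1)} and s1 = √{p0(1 − p0)/n0 + p1(1 − p1)/n1}.

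**The plan's own figures.**
- Cohort: p0 = 0.30, p1 = 0.45, n0 = 538, n1 = 135. Then s0 = 0.0453, s1 = 0.0472 and power = Φ(1.30) = 90.3%. Section 11.1.1 says the sample "would provide 90% power to detect a 50% difference in the primary endpoint", so this agrees.
- Nested trial: 20% vs 42.2% with 67 per arm gives 80.0%, as stated.

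**Day-7 clearance (cohort secondary), no malaria effect.** AL 20% and PA 42.2% are from section 11.1.3. The malaria-negative rate is not given and is assumed to be 20%. With share s of malaria-positives on PA, p1 = 0.20 + 0.222·s. At s = 0.5, s0 = 0.0400, s1 = 0.0434 and power = Φ(0.75).

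| Share on PA | Pooled malaria-positive rate | Spurious RR | Significant |
|---|---|---|---|
| 50% (planning figure) | 31.1% | 1.56 | 77% |
| 40% (assumed) | 28.9% | 1.44 | 60% |
| 30% (assumed) | 26.7% | 1.33 | 40% |

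**Day-14 seroconversion (cohort secondary), no malaria effect.** Section 11.1.3 uses 50% on AL against 25% or 75% on PA, with 10% loss. The malaria-negative rate is assumed to be 50%. The pooled rate is (50 + 25)/2 = 37.5% or (50 + 75)/2 = 62.5%, a spurious RR of 0.75 or 1.25. With 128 vs 509 completers this is significant about 72% of the time. Section 4.3 counts only people seronegative at enrolment; that number is not given, so 72% is an upper figure in this respect.

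**WHO-scale progression (cohort primary).** The protocol gives no PA effect on progression, so reductions of 10%, 20% and 30% are assumed, with half of malaria-positives on PA and RR_PA the risk ratio of PA to AL. With a true malaria effect, p1 = 0.45(1 + RR_PA)/2 against 0.30. With none, p1 = 0.30(1 + RR_PA)/2 against 0.30.

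| Assumed PA reduction | Pooled rate, true 45% vs 30% | Pooled RR | Power | Pooled rate, no malaria effect | Spurious RR | False-positive rate |
|---|---|---|---|---|---|---|
| none | 45.0% | 1.50 | 90% | 30.0% | 1.00 | 5% (nominal) |
| 10% | 42.75% | 1.43 | 80% | 28.5% | 0.95 | 6% |
| 20% | 40.5% | 1.35 | 64% | 27.0% | 0.90 | 10% |
| 30% | 38.25% | 1.28 | 45% | 25.5% | 0.85 | 17% |

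**AL versus malaria-negative only, 45% vs 30%.**
- Crude: about 67 vs 538 completers, power 69%.
- After the 35.6% confounding allowance of section 11.1.1 (708/522): 522 × 0.95 ≈ 496 completers, split about 397 negative and 99 positive, half of the latter on AL. About 49.5 vs 397 gives 57%, against 80% for the pooled contrast.

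**The case against.** Section 11.2.4.1 gives malaria status as an example, leaves the adjusted covariates open and defers detail to the SAP, which was not available for this check. A PA term could appear there. That is fair for the adjusted models. It does not cover the crude model, which the protocol fixes, or the sample size, which treats all 142 malaria-positives as one exposure group.

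The 42.2% is a detectable difference at a sample size set by malaria prevalence, not a prediction. Section 3.2.3 calls clinical benefit unknown, and section 9.2.1.3 states equipoise. This stands: the figures show what follows if PA has that effect. If PA has no effect on an endpoint, that endpoint is not biased.

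Half on PA is a planning maximum. Section 6.2.3.2 excludes pregnant or lactating women, severe disease and recent antimalarial use, among others. This also stands; the 40% and 30% rows show its effect.

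The pooled contrast can be read as malaria under antimalarial treatment, and PA is being rolled out. An AL-only contrast also compares treated malaria with no malaria, and has less power than the pooled one unless PA cuts progression by about 17% or more. These are good reasons not to replace the pooled contrast for the primary endpoint.

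A reader might infer that the cohort and nested-trial questions cannot both be answered. The documents do not support that: the nested comparison is randomised within malaria-positives with arm as its exposure, so pooling in the cohort leaves it untouched.

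**Conclusion.** The mixing is real and follows from the crude model as written. It matters chiefly for the cohort's secondary viral and antibody endpoints. There, the effects on which the nested trial is sized would produce a significant malaria effect that does not exist about 77% of the time for day-7 clearance and up to about 72% for day-14 seroconversion. Those figures assume that malaria-negatives have the AL-arm rate and that half of malaria-positives receive PA.

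A reader might carry the 77% over to the severity primary. That is not supported. On the primary the loss of power (90% to between 80% and 45%) and the false-positive rates (6% to 17%) rest on assumed PA effects that the protocol does not give. The point should be corrected, but it does not invalidate the primary analysis.

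**What to change.** In section 11.2.4, code the cohort exposure in three levels: malaria-negative, malaria-positive on AL, and malaria-positive on PA. Take the malaria effect on clearance, viral load and antibodies from AL versus malaria-negative.

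For the WHO-scale endpoint, keep the pooled contrast as primary and label it as malaria under the trial's mix of AL and PA. Add AL versus malaria-negative as a pre-specified sensitivity analysis, and state its power in section 11.1.1: about 69% crude and about 57% after the confounding allowance.

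No visit, sample or treatment changes, because arm is already recorded. The cost is precision: the AL contrast uses about 67 instead of 135 malaria-positive completers. It also still estimates treated malaria against no malaria, and the text should say so.

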### 11.2.4.2 Continuous endpoints

Continuous endpoints will be summarised using the number of subjects (n), mean, standard deviation (SD), geometric mean (95% CI), minimum, median (50th percentile), 25th and 75th percentiles and maximum by treatment group. For continuous endpoints with single measurements, a GLM model with a normal distribution and identity link function will be used, with the stratification factors 'site' and 'presence of symptoms' as covariates in the crude models and with additional co-

variates in adjusted models. Results will be expressed as the mean differences with their two-sided 95% CIs will be derived from the GLM model. For continuous endpoints with repeated measurements, a GLMMIX with the identity function and normal distribution will be used.

Non-normally distributed data will be transformed to obtain an approximately normal distribution. For example, antibody titres to COVID-19 will be summarised by geometric mean (the Geometric Mean Titre or GMT) (95% CI) by group, and groups compared using the Geometric Mean (Titre) Ratio (GMTR, or GMR) and associated 95% CIs (see also 11.2.4.4, Immunological responses, below).

If variables do not attain a normal distribution after transformation, results will be expressed and the median and 25% and 75% percentile by group and compared using the Wilcoxon rank-sum test.

For the analysis of the disease progression and clinical scales including the WHO clinical progression scale and the FLU-PRO scales, we will use change scores (95% CI) defined as the mean difference between the score at enrolment and the score by defined timepoints, or the maximum score achieved.

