### 4.2 COVID-19 COHORT (N~708)

| Primary objective                                                                                                                                                                       | Primary endpoint                                                                                                                                                                                                                                                                                                                                                                                                          |
|-----------------------------------------------------------------------------------------------------------------------------------------------------------------------------------------|---------------------------------------------------------------------------------------------------------------------------------------------------------------------------------------------------------------------------------------------------------------------------------------------------------------------------------------------------------------------------------------------------------------------------|
| 
 
To determine if malaria infection affects COVID-19 severity
 
                                                                           | 
 
Comparison of the severity of COVID-19 by day-28 in cases with and without malaria using the WHO clinical progression scale
 
                                                                                                                                                                                                                                             |
| Secondary objectives                                                                                                                                                                    | Secondary endpoints                                                                                                                                                                                                                                                                                                                                                                                                       |

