## 16.4 APPENDIX IV. WHO clinical progression scale

Figure 6: WHO clinical progression scale

| Patient State                  | Descriptor                                                                             | Score |
|--------------------------------|----------------------------------------------------------------------------------------|-------|
| Uninfected                     | Uninfected; no viral RNA detected                                                      | 0     |
| Ambulatory mild disease        | Asymptomatic; viral RNA detected                                                       | 1     |
|                                | Symptomatic; independent                                                               | 2     |
|                                | Symptomatic; assistance needed                                                         | 3     |
| Hospitalised: moderate disease | Hospitalised; no oxygen therapy*                                                       | 4     |
|                                | Hospitalised; oxygen by mask or nasal prongs                                           | 5     |
| Hospitalised: severe diseases  | Hospitalised; oxygen by NIV or high flow                                               | 6     |
|                                | Intubation and mechanical ventilation, $pO_2/FiO_2 \geq 150$ or $SpO_2/FiO_2 \geq 200$ | 7     |
|                                | Mechanical ventilation $pO_2/FiO_2 < 150$ ( $SpO_2/FiO_2 < 200$ ) or vasopressors      | 8     |
|                                | Mechanical ventilation $pO_2/FiO_2 < 150$ and vasopressors, dialysis, or ECMO          | 9     |
| Dead                           | Dead                                                                                   | 10    |

ECMO=extracorporeal membrane oxygenation.  $FiO_2$ =fraction of inspired oxygen. NIV=non-invasive ventilation.  $pO_2$ =partial pressure of oxygen.  $SpO_2$ =oxygen saturation. \*If hospitalised for isolation only, record status as for ambulatory patient.

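### The WHO progression and FLU-PRO scales are analysed as mean change from enrolment without the enrolment score as a named covariate; for the supportive severity analyses this misfits the ordinal scale and can cost precision

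*Protocol*

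**What the plan says.** Section 11.2.4.2 of the protocol sets the method for continuous endpoints. For single measurements, "a GLM model with a normal distribution and identity link function will be used". Two covariates are named for its unadjusted version, which is fitted "with the stratification factors 'site' and 'presence of symptoms' as covariates in the crude models". Adjusted models add further covariates that are not listed. Variables that stay non-normal after transformation are to be summarised by medians and quartiles and compared by the Wilcoxon rank-sum test.

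The last paragraph of that section then deals specifically with disease progression and the two clinical scales, WHO and FLU-PRO. Its rule for them is: "we will use change scores (95% CI) defined as the mean difference between the score at enrolment and the score by defined timepoints". It allows the highest score reached as an alternative to the score at a timepoint.

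Appendix IV (section 16.4) gives the WHO scale as 11 ordered states scored 0 to 10. Score 1 is asymptomatic, 2 and 3 symptomatic and ambulatory, 4 is "Hospitalised; no oxygen therapy", and 10 is death.

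Section 4.2 words the cohort primary endpoint as "Comparison of the severity of COVID-19 by day-28 in cases with and without malaria using the WHO clinical progression scale". Section 11.1.1 makes it specific for the sample size: the proportion who worsen by at least one severity category by day 28. Section 11.2.4.1 assigns log-binomial regression to single binary measurements, "including for the binary primary endpoints of the screening study (cross-sectional survey, source population), COVID-19 cohort study and the nested malaria treatment trial".

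**The concern.** Three things are doubtful in the scale paragraph.

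- **Equal steps.** A mean change gives every one-point move the same weight, wherever it occurs on a scale that runs from no detectable virus to death.
- **Two outcomes.** Change to a timepoint and change to the maximum are different quantities, and the text does not choose between them.
- **No enrolment score.** A raw change score subtracts the enrolment value with a coefficient fixed at 1. Estimating that coefficient instead is at least as precise in a randomised comparison.

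At stake is how far the supportive severity results can be interpreted, and how precise they are, in the cohort and (through section 11.2.5.2, which carries the same methods over) between the trial arms.

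**Working it through.** **1. The plan's own figures.** Cohort, 45% vs 30%, 1:4, two-sided 0.05, pooled-variance formula:

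n = [1.960·√(1.25·0.33·0.67) + z·√(0.45·0.55 + 0.30·0.70/4)]² / 0.15²

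- 90% power (z = 1.282): n = 134 malaria-positive, 670 in all, and 670/0.95 = 706 (stated: 673 completers, 708 enrolled). Power at 135 vs 538 is 90.3%.
- 80% power (z = 0.842): n = 99, 495 in all, and 495/0.95 = 522 (stated: 522).
- Nested trial, 20% vs 42.2%, 67 vs 67 completers: power 80.0% (stated: 80%).

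These reproduce. They belong to binary endpoints, so the change-score paragraph does not affect them.

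**2. Equal steps against the protocol's own categories.** Section 11.1.1 counts progression as asymptomatic or mild to at least moderate, moderate to severe, or severe to death. With the scores in Appendix IV:

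| Move | Change score | Progression under 11.1.1 |
|---|---|---|
| 1 to 2 | +1 | no |
| 1 to 3 | +2 | no |
| 3 to 4 | +1 | yes |
| 9 to 10 | +1 | yes |

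In the mean, one death from score 2 (10 − 2 = +8) weighs the same as eight people going from asymptomatic to symptomatic.

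**3. Timepoint or maximum.** Take a participant who enters at 2, is admitted on oxygen (5) and scores 1 on day 28. The change to day 28 is 1 − 2 = −1, an improvement. The change to the maximum is 5 − 2 = +3, a worsening. The two permitted definitions can differ in sign for the same person.

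**4. Precision in the randomised comparison.** Let r be the correlation between enrolment and follow-up score, and k the enrolment SD divided by the follow-up SD. In units of the follow-up variance, and before any other covariate:

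- raw change: 1 + k² − 2rk
- follow-up adjusted for enrolment score: 1 − r²

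The difference is (k − r)², which is never negative, so raw change is never the more precise. The ratio of the two is the factor by which raw change inflates the number of patients needed. With k = 1 it reduces to 2/(1 + r). The documents give neither r nor k, so both are assumptions:

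| | r = 0.3 | r = 0.5 |
|---|---|---|
| k = 1.0 | 1.40/0.91 = 1.54 | 1.00/0.75 = 1.33 |
| k = 0.7 | 1.07/0.91 = 1.18 | 0.79/0.75 = 1.05 |
| k = 0.5 | 0.95/0.91 = 1.04 | 0.75/0.75 = 1.00 |

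**5. Allowing for the symptom covariate.** Symptom status separates score 1 from 2 and above, so it recovers part of the loss. An illustrative simulation assumed enrolment scores of 50% at 1, 30% at 2, 10% at 3, 7% at 4 and 3% at 5, with k = 1. The variance of the enrolment-adjusted analysis relative to change adjusted for symptoms was 0.829 at r = 0.3 and 0.887 at r = 0.5. The inflation is therefore 1/0.829 = 1.21 and 1/0.887 = 1.13.

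**6. What the upper figures would mean for power.** With 67 vs 67 completers, an assumed effect of 0.4 follow-up SD, k = 1 and no symptom covariate, power is 50% for raw change against 68% adjusted at r = 0.3, and 64% against 76% at r = 0.5. This is the unfavourable end of the range.

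**The case against.** **Competing primaries.** A reader might infer from the loose wording of section 4.2 that the cohort has two primary analyses, one binary and one on mean change. The documents do not support that. Section 11.1.1 defines a binary endpoint, section 11.2.4.1 calls the cohort primary binary and gives its model, and section 11.2.4.2 never calls the change score primary.

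**A mean driven by a few deaths.** This is also tempting, but the protocol gives no expected mortality. Its assumptions imply 0.30 × 538 + 0.45 × 135 ≈ 222 progressors, and nothing shows that deaths would dominate the mean. What stands is the equal-step weighting itself.

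**The 1.54 and 1.33.** They need equal SDs and ignore the symptom covariate. If most participants start low on the WHO scale and can move as far as 10, the enrolment SD may well be the smaller, and much of the penalty goes. The figures are an upper part of a range, not an estimate.

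**The cohort.** The formula is for randomised groups. Malaria-positive and malaria-negative patients may differ at enrolment, so change and baseline-adjusted analyses can estimate different quantities there. Wasted precision is not the right description for that comparison.

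**The nested trial.** Its primary is day-7 viral clearance. Its severity outcome in section 4.3 is a secondary severity index score, not stated to be the WHO scale.

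**Left to the SAP.** Detail may indeed be deferred, and the unlisted covariates of the adjusted models could include the enrolment score. If they do, the precision loss disappears from those models, because change adjusted for the enrolment score gives the same group contrast as follow-up adjusted for it. But section 11.2.5.2 makes covariate-adjusted analyses secondary in the trial, and the scale paragraph itself fixes a mean change.

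**The rank-test fallback.** "If variables do not attain a normal distribution after transformation" is a general condition placed before the specific sentence on the scales. A rank test applied to change scores would still depend on step size.

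**Conclusion.** The point holds for the secondary or supportive severity analyses and no further.

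For the WHO scale, mean change is a poor fit: it contradicts the severity categories that the protocol uses for its own primary endpoint and leaves the outcome itself open between timepoint and maximum. That part needs no assumed figure. The argument from death applies to this scale only, not to FLU-PRO.

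For both scales, leaving out the enrolment score can only lose precision in the randomised comparison. The inflation is 1.33 to 1.54 with equal SDs, r of 0.3 to 0.5 and no symptom covariate. It is about 1.0 to 1.2 if the enrolment SD is 0.5 to 0.7 of the follow-up SD, and about 1.1 to 1.2 in the illustrative simulation with the symptom covariate. All of these rest on values that the documents do not give.

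**What to change.** In section 11.2.4.2, replace the change-score sentence with the following:

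- **WHO scale:** the worst score from enrolment to day 28, with death as the worst category, analysed by an ordinal model (for example proportional odds) adjusted for enrolment score and site. The symptom stratum adds little here, since asymptomatic is score 1.
- **FLU-PRO:** the follow-up score, with its enrolment score, site and symptom stratum as covariates.
- **Cohort:** keep the planned adjustment for confounders, and state that change and baseline-adjusted analyses can answer different questions when the groups differ at enrolment.

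The cost is wording and one assumption to check, proportional odds. The Schedule of Activities already places the scale questions on Day 1, so no extra visit, sample or participant is needed.
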